#### Safety

The US FDA raised concern about prolonged Mg^++^ use in pregnancy (http://www.fda.gov/downloads/Drugs/DrugSafety/UCM353335.pdf). This was prompted by 18 reported cases of fetal and neonatal bone demineralization and fractures following long-term in utero exposure to intravenous over a mean of 9.6 weeks, at a mean total cumulative maternal dose of 3700 g. This adverse outcome was not seen in prior RCTs of 24–48 hour intravenous Mg^++^ sulphate for fetal neuroprotection (n = 6145 infants) [38,39] or for the prevention of eclampsia in mothers with preeclampsia (n = 11,444 women, including 3283 children followed to 18 months of age) [40]. The latter level I evidence does not negate the risk of prolonged intravenous Mg^++^ to fetal bone development, but the level IV data about potential harm are sparse and reflect very high doses of intravenous Mg^++^ sulphate.

At high intravenous doses of Mg^++^ sulphate, maternal side effects (nausea, cutaneous flushing, lassitude and muscle weakness) are common [38-40], essentially bordering between a therapeutic vs. a toxic effect. Mg^++^ intoxication causes a reduction in serum calcium concentration, leading to rapid decline in maternal serum parathyroid hormone (PTH) concentration – that is, hypocalcaemia may be partly due to the suppressive effects of acute hypermagnesaemia on PTH secretion [41]. Intravenous Mg^++^ sulphate crosses the placental barrier, which may neuroprotective effect the very preterm fetus, including a reduction in the risk of cerebral palsy, without increasing the risk of perinatal death [40,42]. While 300 mg of Mg^++^ citrate contains 12.4 mmol of Mg^++^, a fair amount is not absorbed, whereas intravenous MgS04 has near-100% bioavailability. With oral Mg^++^ therapy, the normal serum Mg^++^ level is 0.75 to 0.95 mmol/L. In one RCT of 4 weeks of supplemental oral Mg^++^oxalate (400 mg twice daily) in middle-aged non-pregnant adults, serum Mg^++^ levels only changed from 0.84 to 0.89 mmol/L [43]. In a second RCT of 16 weeks of Mg^++^ chloride (2500 mg per day) among non-pregnant adults with diabetes mellitus, serum Mg^++^ levels changed from 0.64 to 0.74 mmol/L [44]. In contrast, among pregnant women who receive intravenous Mg^++^ sulphate – whether as a tocolytic agent in preterm labor, for preeclampsia or for fetal neuroprotection – serum Mg^++^ levels rapidly rise to sustained concentrations of 2.0 mmol/L or more [45,46]. Certainly, acute neonatal depression is positively correlated with maternal serum Mg^++^ concentration in women administered intravenous Mg^++^ sulphate [47]. It is highly unlikely that our proposed dose of Mg^++^citrate 150 mg twice daily can increase maternal (or fetal) serum Mg^++^ concentration to even 50% of that seen when intravenous Mg^++^ sulphate is used in pregnancy.

One of the main determinants of maternal Mg^++^ handling is renal function, including after oral Mg^++^ administration [47,48]. Thus, as a safety measure in our proposed RCT, we will measure maternal serum creatinine concentration at 12–20 weeks gestation. We will deem ineligible any woman whose estimate glomerular filtration rate (eGFR) is under 60 mL/min/1.73 m^2^.

In terms of infant safety, we will assess for the presence of hypocalcemia at birth, defined as a total serum calcium concentration in the umbilical cord below 10 mg/dL. These measures will be obtained in all neonates of BRAMAG enrolled mothers who deliver within IMIP and the Dom Malan Hospital. We will also assess for the presence of neonatal osteopenia by plain X-ray examination of all newborns admitted to the neonatal intensive care unit (and who receive a routine chest X-ray as part of their care). It is expected that around 5% of all newborns studied (150/3,000) will have a chest X-ray. Radiological markers of osteopenia will be assessed on these plain radiographs by a radiologist.

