#### Randomization scheme

Participants will be randomized in a 2:1 fashion to either Mg^++^ citrate or placebo. Block randomization will be used to ensure a balanced number of participants in each group at any time during the study.

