#### Data analysis and sample size

All outcomes will be analyzed by intention to treat (ITT), using logistic regression analysis. The main effects sizes for each outcome will be expressed as a rate (95% CI) and odds ratio (95% CI).

At the time of study entry, on the day of randomization, all women will undergo a measured serum Mg^++^ and creatine concentration. Any woman whose serum Mg^++^ concentration is over 9.5 mmol/dL, or whose estimated glomerular filtration rate (eGFR is under 60 mL/min/1.73 m^2^, will be excluded from the trial, and will not be counted in the ITT analysis. Otherwise, all other randomized participants will be included in the ITT analysis regardless of whether they complete the trial.

An efficacy analysis (on-treatment) analysis will be done for each study outcome, wherein women who were adherent with at least 80% of their dispensed tablets will be analyzed.

At a sample size of 1000 women assigned to placebo and 2000 women assigned to Mg^++^ citrate, with power of 80% and a 2-sided P-value of 0.05, we will be able to detect at least a 22% relative risk reduction in the primary perinatal composite outcome, assuming a primary perinatal composite outcome rate of 18% in the placebo group and 14% in the Mg^++^ group. In Recife there are 25,000 births a year. Of these 25,000, at least 30% (7,500) would attend one of the study prenatal clinics, & of those 7,500, 60% (4,500) would meet ≥1 of the eligibility criteria. With a participation rate of 50%, 2,250 women can be recruited in a year, thus requiring 1.25 years to recruit all women, and 2 years ascertain all primary outcome events.

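### Cord calcium, the only infant safety measure planned for all infants born at the two hospitals, is reduced to a yes/no at an unsourced 10 mg/dL limit; comparing it as a continuous value costs almost nothing and recovers power

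*Protocol article*

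**What the plan says.** The Safety section of the protocol article gives the reason for looking at calcium: "Mg^++^ intoxication causes a reduction in serum calcium concentration". For infants it then sets one calcium outcome, hypocalcaemia at birth, "defined as a total serum calcium concentration in the umbilical cord below 10 mg/dL". On coverage it says: "These measures will be obtained in all neonates of BRAMAG enrolled mothers who deliver within IMIP and the Dom Malan Hospital".

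The other infant safety measure, osteopenia on plain X-ray, reaches only infants in intensive care who have a routine film: "It is expected that around 5% of all newborns studied (150/3,000) will have a chest X-ray". Cord calcium is therefore the only infant safety measure planned for all infants born at the two hospitals.

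The section on data analysis and sample size says that all outcomes are analysed by intention to treat with logistic regression and expressed as rates and odds ratios with 95% CIs. The article gives no mean, SD, percentile or reference range for cord calcium, no expected rate of hypocalcaemia, and no source for the 10 mg/dL limit. The normal range quoted in the Safety section is for serum magnesium.

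**The concern.** A laboratory value that is continuous and measured on up to 3,000 infants is turned into a yes/no at a limit whose basis the reader cannot check. This has two consequences.

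- **Loss of information.** If magnesium lowers calcium a little in most infants, a proportion below one limit is a weaker signal than a difference in means, wherever that limit lies.
- **Dilution.** If magnesium harms only a few infants, who end up with clinically low calcium, every unaffected newborn under 10 mg/dL adds noise to the comparison.

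Either way, similar rates in the two arms could be read as reassurance when the measure was less sensitive than the samples allowed. This matters because the same section discusses fetal bone demineralisation after prolonged magnesium exposure, and cord calcium is the broadest infant check the article offers.

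**Working it through.** **Inputs from the article.** The section on data analysis and sample size gives arms of 1,000 (placebo) and 2,000 (magnesium), which is the 2:1 allocation of the randomization section, a two-sided level of 0.05 and planned power of 80%. The planning rates, 18% and 14%, are for the primary perinatal composite. The article states no rate, power or sample size for hypocalcaemia. All calculations use 1,000 versus 2,000 infants. Fewer will have a cord sample if some mothers deliver elsewhere, so the powers below are upper values.

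**1. Check of the formula on the plan's own figure (primary perinatal composite).** With p̄ = (0.18 + 2 × 0.14)/3 = 0.1533, the placebo arm needs

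n = [1.96 √(p̄(1 − p̄) × 1.5) + 0.84 √(0.18 × 0.82 + 0.14 × 0.86/2)]² / 0.04² = 975.

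Power at 1,000 versus 2,000 is 81%, so the stated 80% is reproduced. This validates the formula only; it says nothing about calcium.

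**2. Small shift in all infants, continuous comparison.** In SD units, SE = √(1/1000 + 1/2000) = 0.0387. For a shift of 0.1 SD, power = Φ(0.1/0.0387 − 1.96) = Φ(0.62) = 73%. The shift detectable with 80% power is 2.80 × 0.0387 = 0.11 SD.

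**3. The same shift, yes/no comparison.** If a share p of placebo infants lies below the limit, the magnesium share is Φ(Φ⁻¹(p) + 0.1) under a normal model. Power is from the two-proportion formula with pooled variance under the null:

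| Placebo share below limit | Magnesium share | Power |
|---|---|---|
| 2.5% | 3.1% | 16% |
| 5% | 6.1% | 23% |
| 10% | 11.9% | 33% |
| 30% | 33.6% | 50% |
| 50% | 54.0% | 54% |
| 70% | 73.4% | 50% |
| 90% | 91.6% | 32% |

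The maximum over all limits is 54%, against 73% for the means. No knowledge of the true cord mean is needed for this comparison.

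**4. Harm confined to a few infants.** Assume clinically low calcium in 1% of placebo and 3% of magnesium infants, all of them below the limit. Let the limit also label a share b of the unaffected. The observed rates are then 0.01 + 0.99b and 0.03 + 0.97b:

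| b | Placebo | Magnesium | Power |
|---|---|---|---|
| 0 | 1.0% | 3.0% | 96% |
| 2% | 3.0% | 4.9% | 72% |
| 5% | 6.0% | 7.9% | 47% |
| 8% | 8.9% | 10.8% | 35% |
| 20% | 20.8% | 22.4% | 17% |
| 50% | 50.5% | 51.5% | 7% |

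**5. What b is at 10 mg/dL.** The documents do not say. With b = Φ((10 − mean)/SD), assumed means of 9.5 to 11.5 mg/dL and SDs of 0.5 to 1.2 mg/dL, it runs from 0.1% (mean 11.5, SD 0.5) to 84% (mean 9.5, SD 0.5).

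**6. What the mean can do under step 4.** If 2 extra infants per 100 each fall by 3 SD (assumed), the mean moves 0.02 × 3 = 0.06 SD, and power is Φ(0.06/0.0387 − 1.96) = 34%. At 2 SD it is 18%, and at 5 SD 73%. The mean alone therefore does not cover a rare harm, so the lower percentiles and a checked limit are needed as well.

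**The case against.** A reader might infer that 10 mg/dL lies near the middle of ordinary cord values, so that the outcome labels a large share of healthy newborns and cannot detect real hypocalcaemia. The documents support neither part.

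- They contain no cord calcium distribution. Step 5 shows that the labelled share may be negligible or very large, depending on what is assumed.
- A central limit would not be blind. For a uniform shift of 0.2 SD, power is about 98% if 50% or 30% of placebo infants lie below the limit, but only about 52% if 2.5% do. Against a uniform shift, moving the limit down to a lower reference value would by itself reduce power. For that reason the limit should be checked rather than simply replaced.

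There is also a case that this is analysis detail. Hypocalcaemia is not among the primary or listed secondary outcomes, no sample-size statement depends on it, and means and percentiles of a laboratory value often sit in an analysis plan that is not shown. The lower importance stands. The argument that the article leaves the analysis open is weaker, since the article itself defines the outcome as yes/no and states a rate and odds-ratio analysis for all outcomes. If that sentence is meant only for the outcomes in Table 2, or if the full plan already compares calcium as a continuous value, the first half of the point is met. The missing basis for the limit remains.

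**Conclusion.** The point holds as a cheap improvement. As written, the calcium outcome discards information. At 0.1 SD, power is at most 54% against 73% for the continuous value. This assumes roughly normal values with equal SD in the two arms, and a sample from every infant.

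If the harm is a rise in clinically low calcium from 1% to 3%, a limit that also labels 5% to 8% of unaffected newborns cuts power from 96% to about 47% to 35%. Both the 1% and 3% rates and the 5% to 8% share are assumptions. Whether 10 mg/dL is well or badly placed cannot be judged from the documents, only that they give no basis for it. No claim about the primary outcomes or the sample size is affected.

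**What to change.** - Make the between-arm difference in mean cord total calcium, with its 95% CI, the main calcium safety comparison, and report the lower percentiles by arm.
- Before unblinding, check the 10 mg/dL limit against the study laboratories' cord reference range and state the source. This review proposes no other limit.
- Keep any proportion below a limit as a supporting summary, with its rate and odds ratio as now planned.

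The samples are already planned, so the change is to wording. The cost is slightly more analysis and reporting work.

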## Discussion

We expect that oral Mg^++^ citrate supplements will lower the risk of preterm birth, perinatal mortality and neonatal morbidity, SGA, and will also positively impact on maternal morbidity and mortality. Thus, the intervention might not only save lives, but lower maternal and early childhood disability.
